#### Index tests

The index tests under investigation (see table 3) will include all diagnostic tests that are recommended by the Dizziness Guideline of the Dutch College of GPs.^6^ This list of tests will be complemented with diagnostic tests for vertigo that were assessed during a systematic review (phase I VERDI) and were deemed appropriate for use in general practice by experts in an international Delphi procedure (phase II). During history taking, we will record sociodemographic characteristics (age, sex, education, partner status, cultural background), smoking habits, alcohol intake, current use of medication, medical history and vertigo characteristics (onset, duration, frequency, triggers, associated symptoms).^6^ Additionally, the patient will be asked to fill out the shortened version of the Dizziness Handicap Inventory (DHI-S), in order to investigate impairment due to vertigo.^33^

**Table 3 T3:** All index tests (history taking and physical examination)

**Sociodemographic characteristics**	**History taking**
*General patient characteristics*	*Vertigo characteristics*
Age	Onset
Sex	Duration
Education	Frequency
Partner status	Associated symptoms
Cultural background	Triggers
*Intoxications*	*Questionnaire*
Smoking habits	Shortened version of the Dizziness Handicap Inventory
Alcohol intake	
*Medical characteristics*	
Medication use	
Medical history	
**Physical examination**	
*Cardiovascular examination*	*Orienting neurological examination*
Pulse	Nystagmus examination
Blood pressure	Visual field examination*
Orthostatic hypotension test*	Dysarthria
Heart auscultation*	Diplopia
	Dysphagia
*Vestibular examination*	Ataxia
Dix-Hallpike manoeuvre	Walking pattern
Supine Head Roll	Sensory system
	Motor system
*ENT examination*	
Otoscopy	*Acute vestibulopathy*
	HINTS Plus exam*

*On indication.

During the physical examination, we will perform measurement of pulse and blood pressure, orthostatic hypertension test on indication (ie, vertigo provoked by standing up and combined with a tendency to fall),^6^ heart auscultation on indication (ie, vertigo provoked by exercise),^6^ nystagmus examination with Frenzel glasses, orienting neurological examination (dysarthria, diplopia, dysphagia, ataxia, walking pattern, motor system and sensory system), visual field examination on indication (ie, (partial) loss of vision),^6^ otoscopy,^6^ the Dix-Hallpike manoeuvre,^31^ the Supine Head Roll^34^ and the HINTS Plus exam on indication (ie, suspicion of vestibular neuritis, ie, subacute or acute spontaneous vertigo with nausea/vomiting and unsteadiness).^25 35^ The duration to perform all index tests will be 30–45 min, depending on the number of tests to be performed.

#### Reference standard

During this study, we will compare each index test with its respective reference standard. Researchers investigating the diagnostic accuracy of a test often encounter ‘no gold standard situations’: situations where the reference standard is not available for all patients, where the reference standard is imperfect or where there is no accepted reference standard.

Consensus or panel diagnosis, an example of a constructed reference standard, is an attractive alternative if a generally accepted reference standard does not exist and multiple sources of information have to be interpreted to reach a diagnosis. In a consensus diagnosis, a group of experts determines the presence or absence of the target condition in each patient based on multiple sources of information. These sources can include general patient characteristics, signs and symptoms from history and physical examination, and other test results.^24^

We will focus on five target conditions that account for more than 95% of vertigo diagnoses in general practice: (1) BPPV, (2) vestibular neuritis, (3) Ménière’s disease, (4) VM and (5) central causes of vertigo.^7^ As these five target conditions have a different pathophysiology and all lack a generally accepted reference standard, we will use consensus diagnosis as reference standard. Data for each patient, including history, physical examination and additional tests as recommended by international guidelines,^1 11 25 29 31 32^ will be recorded on a standardised form within Castor (see the Data collection section) and independently reviewed by a neurologist and otorhinolaryngologist. In case of disagreement, a third reviewer (neurologist or otorhinolaryngologist) will be invited to reach consensus. The reviewers will not meet, in order to avoid domination.^24^

#### Additional testing

Depending on the history taking and physical examination by the study physician during the home visit, a subset of patients may report symptoms that imply a medical indication for additional testing.

Patients with vertigo accompanied by hearing loss, tinnitus and/or aural fullness will receive pure-tone audiometry within 4 weeks after the home visit.

Patients with daily, non-episodic vertigo lasting over 14 days and substantial dizziness-related impairment (defined as a DHI-S score of ≥12)^33^ will receive state-of-the-art videonystagmography (VNG) within 4 weeks after the home visit.^36–40^ Additionally, patients indicated to undergo the HINTS Plus exam will also undergo VNG.

Prior to receiving VNG, patients will undergo a video Head Impulse Test, the Dix-Hallpike test using Frenzel glasses and the Supine Roll test using Frenzel glasses. During VNG, the function of the vestibular organ will be investigated during several test situations, that is, spontaneous nystagmus, oculomotor examination, rotational testing and caloric testing. The total testing time is about 60–90 min.

It is estimated that around 10% of patients will receive audiometry while around 30% of patients will receive VNG based on additional analyses of the general practice cohort within the DIEP (Dizziness In Elderly Patients study) study.^27^

When a patient displays a ‘red flag’, the study physician will contact the patient’s GP the same day. The study physician will advise the GP to act in accordance with the Dizziness Guideline of the Dutch College of GPs (see table 2), which implies that a patient with a red flag may receive additional testing after being referred. To get a complete testing overview, we will approach the patient’s GP to collect these additional data.

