Each year, a Dutch general practitioner (GP) with a standard practice list size (n=2095 patients) sees about 35 patients with vertigo and/or dizziness, of whom 17 patients with vertigo.^6^ More than 80% of patients experiencing vertigo in the Netherlands, the UK and the USA are primarily treated by their GP and are never referred to a medical specialist.^7–9^ The symptoms of these patients are predominantly caused by peripheral vestibular disease, like vestibular neuritis, benign paroxysmal positional vertigo (BPPV) or Ménière’s disease.^7 10^ Sometimes, vertigo in general practice is caused by vestibular migraine (VM)—a benign diagnosis most GPs are not familiar with.^11^ Incidentally, vertigo in general practice has a central and serious cause such as a cerebrovascular event.^7 10^ Despite the fact that GPs treat the large majority of patients with vertigo, their ‘diagnostic toolkit’ has serious limitations. First, there is no empirical evidence on the diagnostic value of history taking and physical examination for patients with vertigo in general practice, because diagnostic accuracy studies on conditions that may cause vertigo have never been performed in a primary care setting.^12 13^ Second, all recommendations for diagnostic testing in (inter)national guidelines are based on consensus and derivative suboptimal evidence from secondary and tertiary care.^6 14–18^ In particular, the quality of the empirical evidence for the recommended Dix-Hallpike manoeuvre is low due to selection bias (tertiary care patients not representative of patients seen in general practice), verification bias (only part of the study population received the reference test) and incorporation bias (reference test incorporates the result of the index test bias,^6 12 19–24^ while the quality of the empirical evidence for the recommended head impulse test is high but was performed among selected populations with patients not representative of general practice, leaving its value for GPs unclear.^6 12 19 25^

Furthermore, previous research suggests that GP diagnosis can be improved: GPs were able to provide a final diagnosis for 60%–64% of the older patients with vertigo/dizziness,^8 26^ whereas an expert panel could provide a diagnosis for 92% of the patients.^27^ Also, GPs hardly (1%–3%) diagnosed other contributory causes,^8 26^ whereas the panel identified other contributory causes in 46% of the patients.^27^

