Finally, diagnostic errors sometimes have serious consequences. Whereas vertigo and dizziness are the symptoms most tightly linked to missed stroke, no less than 9% of cerebrovascular events are missed at initial emergency department presentation.^28^ Accurate and efficient diagnosis for these patients, although low-prevalent in primary care, may save lives and reduce costs through prompt and appropriate treatment.^29^

We hypothesise that the construction of a diagnostic algorithm for GPs may lead to faster and more targeted treatment, less diagnostic imaging and referral to the emergency department and/or hospital, less prescribing of antivertigo drugs and improvement of the overall outcome for patients with vertigo in general practice.

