### Study design

We will perform a prospective diagnostic accuracy study in general practice (‘How well does test x discriminate between patients with or without target condition y?’). Index tests include both questions during history taking (eg, ‘Is your vertigo accompanied by a headache?’) and diagnostic tests during the physical examination (eg, Dix-Hallpike manoeuvre). Target conditions: (1) BPPV, (2) vestibular neuritis, (3) Ménière’s disease, (4) VM and (5) central causes of vertigo other than VM. We will use the Standards for Reporting of Diagnostic Accuracy 2015 checklist to provide accurate and complete reporting of the results of our diagnostic accuracy study.^30^ Patient recruitment runs from March 2023 until February 2026; the overall study end date is 31 December 2027.

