### Home visit

After successful enrolment, participants will be investigated during a planned home visit by study physicians with clinical experience who received a 3-hour training aimed at optimally performing the index tests according to the current guidelines. During the home visit, the trained study physicians will record all clinical data using an electronic case report form (see the Data collection section). When the study physician has entered the results of the index tests, the electronic case report form will automatically provide an overview of indicated additional diagnostic tests for this individual patient according to the current guidelines.^1 11 25 29 31 32^ In case of symptoms that warrant immediate referral (ie, ‘red flags’ like diplopia, dysphagia, ataxia, facial weakness or numbness, see table 2),^6 19^ the study physician will instantly contact the principal investigator of the study. If necessary, the study physician will contact the participant’s GP to discuss further clinical management/immediate referral.

**Table 2 T2:** ‘Red flags’: serious conditions associated with acute vertigo and/or dizziness, for which GP assessment in the (very) short term or direct referral is necessary (the Dizziness Guideline of the Dutch College of GPs^6^)

Characteristics	Urgent condition(s)
Sudden dizziness with neurological symptoms, such as a combination of vertigo with dysarthria, diplopia, dysphagia or ataxia*; a paresis in one or both body halves, sensibility disorder in one or both body halves or homonymous hemianopia	Cerebral infarction, cerebral haemorrhage, transient ischaemic attack
Acute dizziness paired with simultaneously arisen acute *hearing loss*	Cerebral infarction, cerebral haemorrhage, transient ischaemic attack
Acute dizziness paired with acute, very severe headache or neck pain, whether or not after traumatic head injury	Subarachnoid haemorrhage, vertebral artery dissection
Lightheadedness paired with (almost) *falling/collapse* where a cardiac cause is suspected	(Serious) cardiac arrhythmias
Acute dizziness, headache, nausea, lethargy and prolonged stay in a closed room without ventilation	Carbon monoxide intoxication
Briefly existing dizziness in diabetes mellitus and abnormal behaviour or other indications of hypoglycaemia	Hypoglycaemia

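### Outside test results are described as reaching the panel only after a red flag, itself largely an index finding, so the sensitivity and NPV of these signs for central causes are likely to be biased upward

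*Protocol article*

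**What the plan says.** The Additional testing section of the protocol article sets out a sequence that starts from a red flag: "When a patient displays a ‘red flag’, the study physician will contact the patient’s GP the same day". The GP is advised to follow the national guideline, "which implies that a patient with a red flag may receive additional testing after being referred". The section then closes with "To get a complete testing overview, we will approach the patient’s GP to collect these additional data". The data meant are those of the red-flag patients just described. The article describes no similar query, and no clinical follow-up, for anyone else.

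The Home visit section gives as examples "red flags’ like diplopia, dysphagia, ataxia, facial weakness or numbness, see table 2", and Table 2 adds dysarthria, paresis, sensory loss and hemianopia. Table 3 lists dysarthria, diplopia, dysphagia, ataxia, the sensory and motor systems and visual fields (on indication) among the index tests. Data collection has the electronic form detect red flags once the index tests are entered.

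Under Reference standard, a neurologist and an otorhinolaryngologist independently judge every patient from history, examination and additional tests. Under Participants, GPs give usual care before, during and after enrolment.

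**The concern.** A participant without a red flag may still be referred under usual care and be found to have a central cause. That result would sit in the GP record with no described path to the panel. For a participant with a red flag, the same result would be sought. An index finding therefore partly decides how well its own reference diagnosis is informed. If the panel misses the central cause in the first participant, a false negative for the red-flag signs is recorded as a true negative. Sensitivity and negative predictive value (NPV) for central causes then look better than they are.

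This matters more for central causes than for the other conditions. They set the total of 960, about 48 of them are expected, and the Introduction gives missed stroke as a motive for the study: "no less than 9% of cerebrovascular events are missed at initial emergency department presentation". The later diagnostic algorithm is to be built on these estimates. The bootstrap and kappa analyses cannot detect the problem, because they take the panel label as given.

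**Working it through.** **Inputs from the article (Sample size).** Central causes 5%; N = 960; two-sided 95% CI of total width 0.20, so half-width 0.10. Expected central cases: 960 × 0.05 = 48; others: 912.

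**The plan's own figure.** N = 1.96² × Se(1 − Se) / 0.10² / 0.05. The article does not state the expected Se. Se = 0.85 gives 980. Se = 0.855 gives 953, or 960 if the case count is first rounded up to 48. So 960 is consistent with an unstated sensitivity near 0.85, but cannot be reproduced independently.

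**Bias formula.** Let s be the true sensitivity of having any red flag for a central cause. Let d1 and d0 be the shares of central cases that the panel recognises with and without a red flag. Then

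apparent sensitivity = s·d1 / [s·d1 + (1 − s)·d0].

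If d0 = d1 there is no bias; if d0 < d1 the bias is upward. Set d1 = 1 and m = 1 − d0, and ignore false central labels. This gives

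apparent sensitivity = s / [s + (1 − s)(1 − m)].

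The article gives neither s nor m, so both are assumptions, shown over a range:

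| m | s = 0.60 | s = 0.70 | s = 0.80 | Labelled central cases of 48 (s = 0.70) |
|---|---|---|---|---|
| 0 | 0.60 | 0.70 | 0.80 | 48.0 |
| 0.10 | 0.625 | 0.722 | 0.816 | 46.6 |
| 0.25 | 0.667 | 0.757 | 0.842 | 44.4 |
| 0.50 | 0.750 | 0.824 | 0.889 | 40.8 |
| 0.75 | 0.857 | 0.903 | 0.941 | 37.2 |

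Example: s = 0.70, m = 0.50 gives 0.70 / (0.70 + 0.30 × 0.50) = 0.70 / 0.85 = 0.824.

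**Against the planned precision.** At s = 0.70 the bias is 2, 6, 12 and 20 points at m = 0.10, 0.25, 0.50 and 0.75. It reaches the planned half-width of 10 points when 0.70 / [0.70 + 0.30(1 − m)] = 0.80, that is at m = 0.42.

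**If some red-flag cases are also missed.** With d1 = 0.9, d0 = 0.5 and s = 0.70: 0.63 / (0.63 + 0.15) = 0.808. The bias shrinks slightly but remains.

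**NPV and specificity.** Assume s = 0.60 and specificity 0.95. True negatives are 912 × 0.95 = 866.4, and central cases without a red flag are 48 × 0.40 = 19.2. True NPV = 866.4 / 885.6 = 0.978. At m = 0.50, 9.6 cases move to the true negatives, so apparent NPV = 876.0 / 885.6 = 0.989. The apparent risk of a central cause without a red flag halves, from 2.2% to 1.1%. Specificity barely changes (0.950 to 0.951).

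**The case against.** The strongest reply is that the panel sees a good deal about patients without a red flag. A reader might infer that their central causes are invisible, or that they are judged on the home-visit form alone. The article does not support that. History, nystagmus and neurological findings are recorded for all, and HINTS Plus is done on indication. About 30% of patients are expected to have videonystagmography with oculomotor testing, preceded by a video head impulse test, on triggers unrelated to red flags. The panel includes a neurologist. This stands: it makes m smaller than 1, though it does not show that m is 0.

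A reader might also charge the authors with the very fault they criticise in earlier work, "verification bias (only part of the study population received the reference test". That is not accurate. Here everyone receives the consensus diagnosis, and what differs is the information behind it. Differential verification is the better term. The Discussion concedes that the reference standard depends on index tests, but does not mention this unequal information.

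Third, the size is unknown, and large values of m should not be taken as expected. The 9% missed-event figure in the Introduction comes from emergency departments and is only a rough comparator. If the panel missed 9% of all central cases, every one without a red flag, apparent sensitivity would be 0.70 / 0.91 = 0.77 or 0.60 / 0.91 = 0.66.

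Fourth, no composite red-flag test is named as an outcome. The plan does cover combinations of index tests. For single signs the proportional inflation is the same but smaller in points: with s = 0.70 and m = 0.50, a true 0.20 becomes 0.20 / 0.85 = 0.235.

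Finally, this is a condensed article. It uses neither the word only nor the word imaging in this sentence, and the full protocol may collect these data for everyone. That is possible, but the sentence aims at a complete overview and the route it describes does not deliver one.

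**Conclusion.** As described, the outside information available to the panel for central causes depends on an index result. The sensitivity and NPV of the red-flag signs for central causes are therefore likely, but not certain, to be biased upward. At an assumed true sensitivity of 0.70, the overstatement runs from about 2 points if the panel misses a tenth of central cases without a red flag to 12 points if it misses half and 20 if it misses three quarters. It is zero if such cases are recognised as often as those with a red flag. These figures assume that all red-flag central cases are recognised and that there are no false central labels. The direction rests only on the panel recognising central cases without a red flag less often.

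**What to change.** Change the closing sentence of Additional testing so that, for every participant and at the same fixed time after the home visit, GP-held referral letters, specialist findings and test results are collected and placed on the standardised form before panel review. The time point should be short enough that the results concern the index episode.

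Keep the GP's own diagnosis off the form. Phase V compares GP judgement with the algorithm, and the panel diagnosis should not already contain that judgement if it is used as the reference there.

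Add as a limitation that referral will still be more frequent after a red flag, so equal collection reduces the difference in information without removing it. An empty record does not prove the absence of a central cause.

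The cost is one record query per participant, later panel review and possibly a protocol or consent amendment. Most participants come from one academic practice network, and the dates leave room: "Patient recruitment runs from March 2023 until February 2026; the overall study end date is 31 December 2027", a gap of 22 months. The change affects data collection only, not care. If the full protocol already collects these results for all participants, correcting the sentence is enough.

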### Outcomes

For each target condition, we will quantify the level of agreement between the consensus diagnosis (see the Reference standard section) and the results obtained from individual and combinations of index tests. Subsequently, we will compute a range of diagnostic accuracy measures, including sensitivity, specificity, positive and negative predictive values, as well as positive and negative likelihood ratios, and diagnostic odds ratios (see the Statistical analysis section).

### Sample size

Given (a) the estimated distribution of causes of vertigo in general practice (ie, BPPV 42%, vestibular neuritis 41%, Ménière’s disease 10%, central causes 5%, VM unknown),^7^ (b) the estimated diagnostic accuracy of tests previously studied in secondary/tertiary care and possible feasible in general practice^22 31 41 42^ and (c) a two-sided 95% CI width of 0.20, it can be calculated that n=960 patients with vertigo should be included in the study.^43 44^ The calculated sample sizes per target condition are as follows: BPPV: n=603; vestibular neuritis: n=110; Ménière: n=189, central causes: n=960.^22 41–43^ Given the unknown prevalence of VM in general practice, it is not to possible to provide a reliable individual sample size calculation for VM.

The recruitment of 960 patients will take place during 36 months. During this period, a GP with a standard Dutch practice list size (n=2095 patients) is expected to encounter ±60 patients with vertigo.^6^ When 50% of the potential applicants in the present study will participate, we will need 960/(60*0.50)=32 standard practices to achieve the calculated sample size of 960 participants. Because some practices may enter later in the study or have the wish to participate for a shorter period of time, we will recruit 60 standard practices (or, in case of larger practice list sizes, a lower equivalent).

### Recruitment of participants

The large majority of patients will be recruited from the Academic Network of General Practices of the Amsterdam UMC (ANHA). The ANHA consists of more than 120 practices and almost 600 000 enlisted patients. The respective practices comprise a broad spectrum of practices, including both old and young practices, urban practices and practices with an over-representation of socially deprived people. When a patient with vertigo consults his/her GP, the GP will provide care as usual. At the end of the consultation, the GP will use the inclusion and exclusion criteria to assess whether the patient may be a suitable candidate to participate in the VERDI study. If the patient meets the criteria, the GP will ask if the patient is interested to receive information about the study and whether the research team has permission to contact the patient. When the patient gives permission to be contacted, the GP will hand over the patient information folder and send the patient’s contact details to the research team. The research team will call the patient and provide background information about the VERDI study, answer questions, and, when the patient has the intention to participate, schedule an appointment for a home visit after 48 hours. With a time interval of minimum 48 hours, the research group aims for an optimal balance between ‘sufficient decision time’ on the one hand (ie, enough time for the patient to decide about participation) and ‘reliable diagnosis time’ on the other hand (ie, too much time between initial symptoms and actual execution of diagnostic tests may introduce bias). After 48 hours, a trained study physician will visit the patient at home and provide background information and, if necessary, answer questions. When the patient wants to participate, the study physician will obtain a written informed consent form.

